## Abstract

**Introduction:**

Premature birth is associated with long-term somatic and neurological disorders, including cognitive, social and behavioral impairments. Moreover, the mothers of infants born preterm exhibit a higher prevalence of anxiety and depressive symptoms after birth. Early rehabilitation, developmental care, and parenting support have already been shown to have a positive impact on neurological outcome. However, no randomized controlled study has so far assessed the effects on parenting and long-term neurological outcomes of proprioceptive stimulation to trigger positive brain plasticity in very preterm babies. The CALIN project will therefore investigate the impact of sensory-tonic stimulation (STS) of extremely preterm infants by their parents on child parent interactions, infants' morphological and functional brain development and subsequent cognition (including social cognition), and parents' anxiety and depressive symptoms in the postpartum period.

**Methods and analysis:**

Infants born between 25 and 32 weeks of gestation will be randomly assigned to the “STS + Kangaroo care” or “Kangaroo care” group. The primary endpoint, child and parent interactions, will be rated at 12 months corrected age using the Coding Interactive Behavior system. Secondary endpoints include: 1/functional and anatomical brain maturation sequentially assessed during neonatal hospitalization using electroencephalogram (EEG), amplitude-integrated EEG (aEEG), cranial ultrasound and MRI performed at term-corrected age, 2/social and cognitive outcomes assessed at 15 months, 2, 4 and 6 years, and 3/parents' anxiety and depressive symptoms assessed at 7 ± 1 weeks after birth, using dedicated questionnaires.

**Ethics and dissemination:**

This study was approved by the French Ethics Committee for the Protection of Persons on 18 October 2021. It is registered with the French National Agency for the Safety of Medicines and Health Products (ANSM; no. 2020-A00382–37). The registry number on ClinicalTrials.gov is NCT04380051.

## Introduction

1.

### Background

1.1.

In 2018, the World Health Organization (WHO) estimated that 15 million children are born prematurely each year worldwide. The number of newborns surviving a premature birth has gradually increased over the years (1, 2). However, many of those will exhibit varying degree of neurological impairment. In the recent decades, the clinical and morphological picture of brain insults due to prematurity has changed. Classically, extensive clastic injuries (e.g., cystic necrosis of white matter, large infarction of brain parenchyma) most often led to cerebral palsy and/or moderate to severe cognitive impairment. Since the 1990s, however, their incidence has dwindled, and they have been supplanted by less prominent and more diffuse brain damage leading to the loss of vulnerable cells and impaired brain development (3–5).

Nowadays, the spectrum of neurodevelopmental outcomes of preterm babies broadly includes deficits in language, gross and fine motor skills, behavior, and cognition (especially executive functions and social cognition). The severity of the clinical picture is related to the degree of prematurity (6–12). Many brain areas undergo a sensitive period of development during the third trimester of gestation and after birth, during which sensory input shapes neurological maturation and future function. This is the case of the median prefrontal cortex, temporoparietal junction and posterior temporal sulcus (involved in cognition and social cognition) (13–15), the cerebellum, as well as visual, olfactory and somatosensory pathways (16). Premature birth dramatically modifies the context of this developmental window. During hospitalization, the developing brains of infants born preterm are exposed to stimuli that may be detrimental to their maturation (17) with either too much or too little sensorial input (18). This is referred to as *dystimulation*.

Furthermore, premature birth disturbs early infant-parent interactions, and ultimately relationships with others. Preterm infants are not only separated from their parents, but placed in a stressful, technical, and potentially painful environment. Comorbidities and sedation have a negative physiological impact and reduce their availability for interaction. On the parental side, the idealized postnatal period is replaced by an anxious–and even traumatic–experience (19–21). Parents often express guilt and anxiety about the survival of their child and their parenting skills. A higher prevalence of parental anxiety, postnatal depression and posttraumatic stress disorder has been observed in the mothers of infants born preterm (22), even up to 18 months after birth (23).

Finally, prematurity severely disturbs the ability of both parents and newborns to interact and find reassurance. More than 35% of children born preterm subsequently exhibit insecure attachment behavior in relationships with others (24). Given that studies have demonstrated a longitudinal link between attachment security and cognitive development (25, 26), specially social cognition (27, 28), it seems important to study the effects of disturbed early interactions on child development, and to test the potential of intervention programs to efficiently minimize these effects.

Developmental care has been implemented in many neonatal intensive care units (NICUs) to overcome the difficulties described above. The “Kangaroo mother care” and the “Newborn Individualized Developmental Care and Assessment Program” (NIDCAP) are among the most studied and practiced in the world. Fundamentally, those approaches place the family at the center of the newborn care, promoting affective contact with parents, and aiming at reducing dystimulation and sleep wake cycle interruptions (29). Those methods have shown positive effects on weight gain, sleep wake cycle interruptions electroencephalographic (EEG) activity, duration of hospitalization, some items of long term cognitive development and maternal anxio-depressive symptomatology (30–34). The involvement of parents in care is associated with many benefits: for the parents, it enhances the parenting process, their perception of their child, their sense of competence, and their attachment; for the child, it has a positive impact on cognitive and motor development, on executive function disorders and psychological disorders (31, 35–37).

Several teams are now investigating whether the focused enrichment of infants' sensorial input provides an additional effect to developmental care. Exposure to sounds such as maternal heartbeat, voices and music are promising avenues (38–42). Some studies have documented effect of somesthetic stimulation (43, 44). These interventions variably associate skin contact, massage (sliding on the skin), kinesthetic stimulation (movement of the child's limbs) and positioning. In most experimental protocols, those interventions have been performed one to three times a day, after feeding, during 5 to 10 days, on moderately preterm babies (39). Those interventions were associated with an increase in weight gain, lymphocyte natural killer activity (associated with a reduction of the incidence of late neonatal sepsis), as well as a decrease in pain response. A reduced length of stay in hospital and a better developmental score at 12 and 24 months were reported (43, 45–47). However, studies evaluating longitudinally the effectiveness of early tactile and kinesthetic interventions on several key aspects of extremely preterm children development are still sparse.

### Objectives and hypotheses

1.2.

The overall aim of this study is to assess effect of a sensori-tonic stimulation (STS) provided by parents, associated with kangaroo care, vs. kangaroo care alone, on the quality of parent-infant interactions, parental wellbeing, and ultimately brain maturation and cognitive outcome of infants born preterm.

#### Primary objective

1.2.1.

This study will investigate the benefits of early STS, provided by one of the parents on its infant born preterm on the developing interactions between them. We expect to observe stronger interactions in the dyads who practiced STS + kangaroo care, than in the control group (kangaroo care only).

#### Secondary objectives

1.2.2.

The present work will assess, in children born very preterm, the effect of “STS + kangaroo care” vs. “kangaroo care” alone on: 1/the morphological and functional brain maturation, 2/the precursors of cognitive development at 15 months, 3/psychomotor development at 2 and 4 years, and 4/cognition including social cognition assessed at 6 years of age.

Moreover, this study will assess the impact of the intervention on symptoms of anxiety and depression experienced by the parents of children born preterm.

## Methods

2.

### Design

2.1.

The CALIN study is a prospective, multicentric randomized study. The clinicians who carry out the assessments will be blind to the result of the randomization. Participants will be recruited in French tertiary neonatal centers equipped with Neonatal Intensive Care Units.

### Participants

2.2.

#### Study population

2.2.1.

Children born between very preterm and their parents will be eligible if they meet the following inclusion criteria: 1/the child is inborn, 2/birth between 25 and 32 weeks of gestation and weight over 600 g at birth, 3/the child's hospitalization at the recruiting center is planned until 36 weeks corrected age, 4/the child's parents have parental authority and have agreed to participate in the study by signing the informed consent, 5/the child's parents are available physically and mentally to participate in the study and 6/the child and his/her parents are affiliated to the social security system.

The exclusion criteria are the following: 1/the child is hemodynamically unstable, 2/the child has a suspected comorbidity (e.g., genetic syndrome, congenital malformation, brain injury, skin pathology), 3/the child was born from a multiple pregnancy, 4/the child was born anonymously, 5/the child is to be separated from his/her parents (e.g., assigned to infancy protection services).

If the child's condition does not allow the practice of STS (for example: hemodynamic compromise, enterocolitis), the intervention may be temporarily discontinued until the condition improves. The discontinuation and the resumption of the intervention are decided by the medical staff in charge of the child, who informs and explains the decision to the parents. Newborns will not be excluded from the intervention group.

#### Sample size calculation

2.2.2.

The sample size has been calculated so that a two-tailed test will detect a significant difference in the primary endpoint (Coding infant behavior scale at 12 months corrected age, see below), with a power of 90% and a significance level of 0.05 (alpha value). Forty-eight infants would be required in each group (NQuery 4.0® software). In anticipation of loss to follow-up, the target size has been increased by 20%, such that 60 children will be included in each group, resulting in inclusion of a total of 120 infants.

#### Randomization

2.2.3.

The newborns and their parents will be randomly assigned to either the experimental group or the control group. Those in the experimental group will participate in the STS intervention, in addition to kangaroo care. The control group will benefit from kangaroo care alone. Besides that, the medical and nursing care will be the same, regardless of the outcome of the randomization.

### Intervention

2.3.

Sensory-tonic stimulation (STS) refers to a protocolized, tactile, vestibular and kinesthetic stimulation, provided by a parent to her/his baby born preterm. This proprioceptive stimulation is carried out using an enveloping and continuous touch with a moderate pressure, as described in the literature (48, 49).

STS will be adapted to the newborn's term and level of development, broadly stratified into three stages (25-30, 31–34 and 35–36 corrected age, respectively). The preterm infant is either installed in a microbead baby nest in the incubator or on the changing table, depending on the newborn's usual arrangement and maturity. This position facilitates the sensory-tonic care, the observation of the behavior of the newborn, her/his signs of comfort and discomfort, and her/his state of alertness. At each stage, the stimulation begins with a two-handed enveloping contact with the child lying on his or her back: one hand on the trunk, the other hand supporting the pelvis, with the legs folded. Then, the hands slowly slide under the child's head/neck and pelvis, to lift the child and perform vestibular stimulation with gentle rocking motions. As the child matures, the parent adds hand movements along the child's limbs, then slow flexion-extension movements. The approximate duration of each step is between fifteen seconds and one minute, depending on the baby's tolerance and the step considered. Moving on to each next step requires a favorable state of alertness and the absence of signs of discomfort. As much as possible, the contact and gentle pressure between the hands and the baby's skin are continuously maintained. At all times, if signs of discomfort are observed: a comfortable and calming position is maintained (usually lateral roll-up).

Parents will be coached by a trained, designated professional, initially using a mannequin. They will also be shown a training video and given an illustrated training booklet covering all the steps of STS. They will begin from the 10th day after birth and when the parents feel ready to perform it and will continue until discharge from hospital or 36 weeks corrected age. STS should be carried out 5 times per week, 5-15 min each time. STS will be performed when the newborn exhibits quiet alertness (State 3 or 4 according to Brazelton (50)). The intervention will be interrupted if signs of discomfort are detected in the newborn or his/her parents. Once a week, a trained psychologist or psychomotor therapist will supervise the parent's gestures and discuss his/her experience.

“Skin to skin care” will be practiced without any restriction in both groups, following local policies. In the experimental group, newborns and their parents will participate in STS in addition to kangaroo care. The time, number, duration of each skin-to-skin care or STS will be collected, as well as somatic stability, initial and maximal state of alertness of the baby (51).

Preterm babies will benefit from the usual neonatal intensive care, following the local policies of each center.

### Assessments and outcomes

2.4.

An overview of the different assessments and outcomes is provided in Figure 1.

**Figure 1 F1:**
[figure not shown]
Design of the study, overview of assessments and outcomes.

#### Primary outcome

2.4.1.

The quality of interactions between the very premature infants and their parents will be scored at 12 months corrected age using the Coding Infant Behavior system (CIB) (52). The latter assesses the quality of child-parent interactions by observing the occurrence of behaviors along six dimensions: parental sensitivity, parental intrusion, child's social engagement, child's negative emotionality and engagement, dyadic reciprocity, and negative dyad states. This scale is validated from birth to 3 years of age and has shown a great sensitivity in scoring interactions in many social and/or pathological situations (53). Early CIB scores have previously been correlated with cognitive development (54). We will record two 15 min sequences of child-parent interactions during free play. Observations will be double-quoted by professionals trained to use the CIB, blinded to the randomization group. The main judgment criteria will be the score in “child's social engagement” dimension of the CIB system. The Secondary judgment criteria will be the scores in the other dimensions of the CIB system.

#### Secondary outcomes

2.4.2.

##### Morphological and functional development of the brain

2.4.2.1.

All the data yielded by the following paraclinical examinations will be anonymized and sent to the main investigating center for centralized review. They will be interpreted by two experts for each technique used, blinded to the randomization group.

Serial cerebral ultrasound scans will be performed during the infants' NICU stay, following a standardized protocol. Lesions will be classified: 1/according to the Papille classification for intraventricular hemorrhages, 2/according to the De Vries classification for periventricular leukomalacia (55). Moreover, several two-dimensional measurements will be performed on ultrasound scan to assess brain growth: interhemispheric distance, ventricular width, thickness of motor and somatosensory cortex, diameter of thalami and cerebellum.

Brain magnetic resonance imaging (MRI) will be performed at term-corrected age including a diffusion sequence, following a standardized protocol of acquisition. Imaging will be interpreted according to Kidokoro (56). Moreover, regional brain volumes will be quantified using semi-automatic, post-hoc segmentation.

EEG and amplitude-integrated EEG will be sequentially recorded. Timing of the EEG recordings and their interpretation will follow the guidelines of the French society of electrophysiology (57).

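### Cranial-ultrasound outcomes cover the NICU stay and are compared without a baseline, although STS cannot start before day 10: no bias, but dilution and lost precision

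*Protocol article*

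**What the plan says.** All references are to the protocol article.

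- **Endpoint.** The abstract (Methods and analysis) lists among the secondary endpoints "functional and anatomical brain maturation sequentially assessed during neonatal hospitalization using electroencephalogram (EEG), amplitude-integrated EEG (aEEG), cranial ultrasound and MRI".
- **Scans and measures.** Section 2.4.2.1 says: "Serial cerebral ultrasound scans will be performed during the infants' NICU stay, following a standardized protocol". It continues: "Lesions will be classified: 1/according to the Papille classification for intraventricular hemorrhages, 2/according to the De Vries classification for periventricular leukomalacia". It adds two-dimensional measurements intended to track brain growth. Two experts per technique read the examinations centrally, blinded to group.
- **Start of STS.** Section 2.3, on the parents in the experimental group: "They will begin from the 10th day after birth and when the parents feel ready to perform it".
- **Eligibility.** Section 2.2.1 excludes an infant if "the child has a suspected comorbidity (e.g., genetic syndrome, congenital malformation, brain injury, skin pathology"). On what follows allocation it says: "Newborns will not be excluded from the intervention group".
- **Allocation.** Section 2.2.3: "The newborns and their parents will be randomly assigned to either the experimental group or the control group". The day of randomisation is not given.
- **Analysis.** Section 2.5.2 compares the groups on every secondary outcome by Student, Mann-Whitney, chi-square or Fisher tests. It describes no use of an earlier scan.

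**The concern.** The scanning period and the intervention period do not match. Scans run through the NICU stay, while STS can act only from day 10 and later still if parents are not yet ready. A haemorrhage graded in the first days, or a cerebellar diameter that is small at the outset, cannot have been changed by STS. If such findings enter the two-group tests as they stand, they add events and variance that carry no information about STS.

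What is at stake is how the ultrasound part of the first secondary objective (morphological brain maturation) can be read. A null result could mean that STS has no effect, or that an effect was submerged in findings that came before it. The two-dimensional measures raise the same issue whatever the lesion rate: growth is change from a starting point, and a test on a later measurement alone leaves between-infant differences in starting size in the error term.

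**Working it through.** **Inputs from the article.** 60 infants per arm (section 2.2.2: 48 / (1 − 0.20) = 60), two-sided alpha 0.05, STS from day 10 at the earliest. The article gives no figure for ultrasound lesions, so there is none to reproduce.

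**Assumed inputs, not in the article.** Let p0 be the proportion of included infants with a lesion before day 10, the same in expectation in both arms, from 0 to 30%. New lesions after day 10 are assumed in 20% of controls and 5% of the STS arm.

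**Step 1: is there bias?** The proportion of infants with any lesion during the stay is p0 + (1 − p0) × p_new. If STS does nothing (p_new = 10% in both arms), the expected difference is zero for every p0. Exact enumeration at 60 per arm for p0 from 0 to 30% gives a type I error of 0.022 to 0.031 with Fisher's test and 0.047 to 0.053 with the uncorrected chi-square test. The chance difference between arms in early lesions has standard deviation √(2 × p0 × (1 − p0) / 60): 4.0 percentage points at p0 = 5%, 5.5 at 10%, 7.3 at 20% and 8.4 at 30%. The tests already allow for this variation.

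**Step 2: dilution when STS works and every lesion of the stay counts.** Power = Φ{[Δ√60 − 1.96√(2p̄(1 − p̄))] / √(a(1 − a) + b(1 − b))}, where a and b are the two proportions, Δ = a − b and p̄ is their mean.

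Example, p0 = 10%: a = 0.10 + 0.90 × 0.20 = 0.280 and b = 0.10 + 0.90 × 0.05 = 0.145. So Δ = 0.135, p̄ = 0.2125, and power = Φ[(1.046 − 1.134) / 0.571] = Φ(−0.15) = 0.44.

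| p0 | Control | STS | Difference | Power (formula) | Power (Fisher, exact) |
|---|---|---|---|---|---|
| 0 | 0.200 | 0.050 | 0.150 | 0.70 | 0.63 |
| 5% | 0.240 | 0.098 | 0.142 | 0.55 | 0.46 |
| 10% | 0.280 | 0.145 | 0.135 | 0.44 | 0.35 |
| 20% | 0.360 | 0.240 | 0.120 | 0.30 | 0.23 |
| 30% | 0.440 | 0.335 | 0.105 | 0.22 | 0.17 |

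**Step 3: how much does a day-10 cut recover?** The p0 = 0 row is the best case. It applies after the cut only if infants with an early lesion have new or upgraded lesions at the same rates as the others. At the other extreme they never have a countable event, and the proportions among all 60 are (1 − p0) × 0.20 and (1 − p0) × 0.05. At p0 = 10% these are 0.180 and 0.045, and the same formula gives 0.65 (against 0.44 without the cut). At p0 = 20% they are 0.160 and 0.040, giving 0.59 (against 0.30). The recovered power therefore lies between 0.65 and 0.70, or between 0.59 and 0.70.

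**Step 4: two-dimensional measures.** Let ρ be the correlation between the baseline scan and the last scan, with equal variances. Relative to a test on the last scan alone (1), the variance of the group difference is 2(1 − ρ) for a change score and 1 − ρ² for ANCOVA. ANCOVA is never worse than the change score, because 2(1 − ρ) − (1 − ρ²) = (1 − ρ)² ≥ 0. The change score is worse than no adjustment when ρ is below 0.5. The article gives no ρ.

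**The case against.** A reader might infer that lesions arising before STS would be counted as its effect, producing a false benefit or harm. The documents do not support that. Allocation is random, reading is blinded, and step 1 shows no expected difference and no excess of false positives. Systematic bias would need selection after allocation, for example a brain-injury exclusion applied differently by arm. The article describes nothing of the kind and rules out exclusions from the intervention group.

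Three further objections have weight. First, the scanning schedule is not necessarily the analysis window: the article does not say that every lesion of the stay enters the test, and the full protocol or analysis plan may restrict it. That stands as a limit on certainty. But the analysis the article does state is a direct two-group test, and its stated scanning period is wider than the period of STS. Second, the brain-injury exclusion lowers p0. If inclusion falls close to day 10, most early lesions already suspected are removed and the loss is small; the day of inclusion is not stated. Third, counting events from randomisation is a standard intention-to-treat convention and is valid. That stands too: the case for the cut rests on precision, not validity.

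A growth analysis implicitly needs an early scan, so the investigators may intend one. Nothing in section 2.5.2 says so.

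**Conclusion.** The point holds as a minor one about precision. The stated ultrasound comparison is valid, but it takes in findings that STS could not have influenced and makes no use of the early scans. On the assumed rates, power for lesions drops from about 0.70 to 0.44 or 0.30 when 10% or 20% of included infants have an earlier lesion. These figures illustrate the mechanism and do not forecast this trial: the lesion rates, the effect and the timing of inclusion are all unknown, and a small p0 makes the loss small. The trial is powered for the interaction score at 12 months, which this does not touch. For the two-dimensional measures, the gain from baseline adjustment needs no assumption about lesions and grows with the correlation between scans.

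**What to change.** Redefine the ultrasound outcomes identically in both arms:

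1. Take the last available scan up to day 10 as baseline. A fixed day in both arms keeps the window from depending on when parents chose to start.
2. Count as lesion outcomes only haemorrhage or leukomalacia that is new or upgraded after day 10.
3. For the two-dimensional measures, compare the last scan by 36 weeks between arms by ANCOVA with the baseline scan as covariate, rather than by a raw change score.
4. Report lesions seen up to day 10 as baseline characteristics by arm.

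The cost is wording: the serial scans are already planned and no clinical procedure changes. The downside is fewer countable lesion events. With 60 infants per arm, the lesion comparison should be presented as largely descriptive, with estimates and confidence intervals.

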#### Statistical analysis of secondary outcomes

2.5.2.

All secondary outcomes are quantitative measures. For all these measures, we will compare the scores of the experimental group with those of the control group, according to the distribution of the data, with parametric or nonparametric tests (Student's *t*, Mann-Whitney, chi^2^ or Fisher's exact tests), depending on the application conditions. Correlations will be calculated between quantitative measures.

A *p* value of < 0.05 will be considered statistically significant.

Statistical analysis will be performed with software “R®”(76).

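### Regional brain volumes from the single term-age MRI are compared by an unadjusted two-group test that leaves age at scan in the error term

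*Protocol article*

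**What the plan says.** **Timing of the scan.** Under Morphological and functional development of the brain, the article says that "Brain magnetic resonance imaging (MRI) will be performed at term-corrected age including a diffusion sequence". The only modality which that section ties to the hospital stay is ultrasound: "Serial cerebral ultrasound scans will be performed during the infants' NICU stay". The abstract puts everything into one phrase, "functional and anatomical brain maturation sequentially assessed during neonatal hospitalization using electroencephalogram (EEG), amplitude-integrated EEG (aEEG), cranial ultrasound and MRI performed at term-corrected age". Under Study population, eligibility requires that "hospitalization at the recruiting center is planned until 36 weeks corrected age".

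**What is measured.** Besides a scored reading of the images, "regional brain volumes will be quantified using semi-automatic, post-hoc segmentation".

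**How it is analysed.** The opening of Data analysis names group as the independent variable for everything after the descriptive summary. Statistical analysis of secondary outcomes then covers all secondary measures together: "we will compare the scores of the experimental group with those of the control group, according to the distribution of the data". The tests it lists are Student, Mann-Whitney, chi-square and Fisher. None of them takes a covariate, and age at scan is not mentioned.

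**The concern.** A regional volume measured near term reflects both the infant and the infant's age on the day of the scan. A two-group test treats the second part as noise. Two consequences are possible, and they differ in weight.

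- **Loss of precision.** Any spread in scan age adds to the variance of the volumes, even when the arms are perfectly balanced. A real effect of the intervention becomes harder to see.
- **Bias.** If one arm is on average scanned later, its volumes are larger for that reason alone, and the test attributes the difference to the intervention.

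Brain maturation is listed first among the secondary objectives, so the volume comparison will be read closely. The date of the scan is known for every infant scanned, so the information needed to deal with this costs nothing to collect.

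**Working it through.** The documents give no figure for MRI volumes, so there is none to reproduce. The size has to be shown over assumed ranges.

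**Inputs**
- n = 48 per arm, from Sample size calculation. It was set for the primary endpoint. Using it as the number scanned is an assumption.
- Two-sided 5% test, from the same section and from Statistical analysis of secondary outcomes.
- g, growth of volume per week near term in units of the between-infant SD at a fixed age: 0.3 to 0.5. Assumed.
- s, SD of age at scan in weeks: 0.5, 1 and 1.5. Assumed.
- Systematic difference between arms in mean scan age: zero, or 3 to 5 days. Assumed.

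**Step 1: scan ages balanced between arms.** The variance of the unadjusted volume is multiplied by 1 + g²s², and the effective sample size is 48/(1 + g²s²).

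| s (weeks) | g = 0.3 | g = 0.5 |
|---|---|---|
| 0.5 | 1.0225; n = 46.9 | 1.0625; n = 45.2 |
| 1 | 1.09; n = 44.0 | 1.25; n = 38.4 |
| 1.5 | 1.2025; n = 39.9 | 1.5625; n = 30.7 |

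In terms of power, the effect detectable with 90% power at 48 per arm is (1.960 + 1.282) × √(2/48) = 0.66 SD. For an effect of that size and s = 1 week, power without age at scan falls to 87.4% (g = 0.3) or 82.6% (g = 0.5).

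The type I error stays at 5% here. A chance difference in mean scan age, with standard error s√(2/48), or about 1.4 days for s = 1 week, is already part of the inflated variance.

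**Step 2: mean scan age differs systematically.** Spurious difference = g × days/7.
- g = 0.3, 3 days: 0.3 × 3/7 = 0.129 SD; noncentrality 0.129 × √24 = 0.63.
- g = 0.5, 5 days: 0.5 × 5/7 = 0.357 SD; noncentrality 0.357 × √24 = 1.75.

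With 94 degrees of freedom, the noncentral t distribution gives rejection rates under no treatment effect of about 10% and 41%. With a shift of zero the rate is 5%.

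**Step 3: do the documents imply such a shift?** The abstract and the methods section both attach term-corrected age to the MRI. The methods section links only ultrasound to the stay. No section makes the scan conditional on the infant still being an inpatient, or schedules it at discharge. Step 1 therefore follows from the stated plan whenever scan ages vary, while Step 2 is conditional on something the documents do not state.

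**The case against.** **A stronger reading that fails.** A reader might infer that who is scanned, and at what age, depends on discharge. The abstract can be read as placing MRI within the hospital stay, the stay is secured only to 36 weeks, and the Background says of earlier stimulation studies that "A reduced length of stay in hospital and a better developmental score at 12 and 24 months were reported". The documents do not support this. The abstract's phrase gives MRI its own timing at term-corrected age, in agreement with the methods section, so it is a loose sentence and not a rival schedule. The 36-week criterion is a minimum planned stay, not an end of contact: the trial follows these children to 6 years, and a discharged infant can return for a scan. The Background remark concerns varied earlier interventions, mostly short and in moderately preterm babies. It would matter only if scans tracked discharge.

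**Detail left to other documents.** The width of the scan window may well be in the full protocol, the imaging protocol or the assessment figure, none of which is shown. Its absence is no finding. The same defence does not cover the analysis, because the article is not silent on it: it names the tests and applies them to all secondary measures.

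**Validity of the unadjusted test.** With balanced scan ages, an unadjusted comparison of randomised groups is valid. That stands, and it limits the point to precision.

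**The covariate is recorded after randomisation.** This also stands. If the intervention did influence when infants are scanned, the adjusted estimate answers a different question from the unadjusted one. Nor would adjustment cure selective attendance, which is why the numbers scanned should be shown by arm.

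**Conclusion.** The stated analysis of regional volumes omits age at scan, and a better method is available at almost no cost. Under the assumed growth of 0.3 to 0.5 SD per week, the variance is 2 to 6% too large if scan ages are tightly clustered (SD 0.5 week) and 9 to 56% too large if they spread by 1 to 1.5 weeks. The false-positive rates of 10 to 41% belong only to an assumed systematic shift of 3 to 5 days between arms. Nothing in the documents shows such a shift, and without it the rate is 5%. All these sizes rest on assumed growth rates and scan-age spreads, and on 48 scans per arm.

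This is a modest improvement to one secondary outcome. It does not touch the primary endpoint, and it does not show that the MRI comparison is biased.

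**What to change.** 1. In Statistical analysis of secondary outcomes, take regional volumes out of the general two-group rule. Analyse each with a linear model containing group and postmenstrual age at scan. Keep the unadjusted comparison as a sensitivity analysis and present the two side by side.
2. Report the distribution of age at scan and the numbers scanned and not scanned, by arm.
3. In the abstract, state that MRI is performed at term-corrected age whether or not the infant is still in hospital, so that it agrees with the methods section.

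**Cost.** A few sentences, one covariate derived from the scan date, and one degree of freedom per model. The downside is the one already named: age at scan is recorded after randomisation, so the adjusted result should not be read without the unadjusted one.
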